## Abstract

**Background:**

Breast cancer is the most prevalent cancer among women globally, and surgical procedures continue to be the primary treatment. However, over 50% of patients experience preoperative anxiety due to the unknown and fear associated with surgery. Although drug therapy is commonly used to address this anxiety, its side effects have led to a heated debate regarding its effectiveness. Consequently, non-pharmacological therapies, such as preoperative education, have emerged as an alternative approach to alleviate anxiety. WeChat, a widely popular social media platform, offers a public platform that can potentially be utilized for effective preoperative education. This study aims to evaluate the use of WeChat public platform as a tool for preoperative education in patients undergoing breast surgery.

**Methods:**

This is a prospective, randomized, and controlled trial will involve 392 adult women scheduled for breast cancer resection. Participants will be randomly assigned to either the WeChat education group or the regular group. In addition to regular preoperative visits, the WeChat education group will also watch science videos through the WeChat public platform. The regular group will only receive education from ward nurses during preoperative visits. The primary outcome measure will be the incidence of preoperative anxiety, defined by scores of the State Anxiety Inventory (SAI) exceeding 40 points. Secondary outcome measures include the incidence of severe anxiety (SAI > 44) on the day before surgery, incidence of anxiety 72 h after surgery, incidence of severe anxiety 72 h after surgery, NRS scores for pain at rest and during activity 24, 48, and 72 h after surgery, incidence of nausea and vomiting within 24 h after surgery, subjective sleep score at 1 week postoperatively, quality of life QoR-15 scores at 1 and 3 months postoperatively, incidence of chronic pain at 3 months postoperatively, bowel function recovery, length of hospital stay, and hospitalization expenses.

**Discussion:**

This is the first clinical trial to investigate the use of WeChat public platform for delivering preoperative education on perioperative anxiety in breast cancer patients. By utilizing the renowned WeChat public platform, our study aims to improve patient outcomes by providing video education that explains the disease, surgery, and anesthesia in a more accessible manner, thereby reducing the incidence of perioperative anxiety. If our hypothesis is confirmed, this non-pharmacological approach can be universally acknowledged as a cost-effective and practical method in clinical care. Its application can also be extended to other medical fields beyond breast cancer.

**Trial registration:**

ClinicalTrials.gov, NCT05291494. Registered on 29 December 2021.

**Supplementary Information:**

The online version contains supplementary material available at 10.1186/s13063-024-08071-3.

## Introduction

Breast cancer is the most common form of cancer among women [1] and ranks as the second leading cause of cancer-related deaths [2]. Statistics suggest that 13% of females will develop breast cancer during their lifetime [2]. Surgery remains a crucial component of breast cancer treatment for non-metastasized cases. However, while surgery removes the tumor, it often inflicts significant psychological distress on patients. Previous empirical evidence indicates that 51% of patients experience preoperative anxiety [2], which can lead to various negative consequences. Additionally, postoperative changes in appearance further contribute to patient distress. Research shows that the incidence of moderate to severe anxiety before surgery reaches 53.4% [3, 4]. A study conducted by Rosiek A and his team has linked preoperative anxiety to adverse effects on blood pressure, heart rate, neuroendocrine system, postoperative recovery, and increased dependence on analgesics [5]. Moreover, preoperative anxiety has the potential to induce or exacerbate acute and chronic pain after surgery, as well as cause sleep disorders [6–8], all of which hinder patients’ early recovery. While drug therapy is commonly used to address preoperative anxiety, its clinical application is limited due to side effects such as hypotension, bradycardia, slow breathing, nausea, vomiting, allergies, and even shock [9, 10]. Recent studies have also associated the use of anti-anxiety drugs with longer hospital stays and postoperative adverse events, including reoperation, infection, and cardiovascular and cerebrovascular events [11]. Consequently, non-pharmacological therapies, such as preoperative education, have emerged as viable option for anxiety relief, gaining significant attention [12–14]. Specifically, preoperative education manuals have demonstrated benefits in decreasing patient anxiety levels [15], as highlighted by the research of Kiyohara and Harkness [16, 17]. However, these methods have inherent limitations related to time, space, and patients’ educational backgrounds. Patients may struggle to recall information provided by ward nurses or face difficulties in achieving a complete understanding, particularly among older individuals. Moreover, accessibility to education is restricted by availability and convenience. Therefore, the development of education videos has gained importance. As early as 1989, Herrmann successfully utilized video for preoperative education in cardiac catheterization procedures to reduce anxiety levels [18]. However, time and space constraints still posed challenges. Hence, it is crucial to identify a more convenient, non-pharmacological therapy based on video to effectively reduce preoperative anxiety.

WeChat is a comprehensive application that integrates social media, instant messaging, mobile payment, and e-commerce functions. It is widely regarded as one of the most popular social media platforms globally, surpassing the combined login time of the top four social platforms in American platforms [19]. In China, WeChat has become an indispensable part of daily life and boasts over 1 billion monthly active users [19]. Surprisingly, more than one third of users spend more than 4 h on the platform each day. In 2017 alone, an average of 38 billion messages were sent through WeChat daily, with 68 million of them being videos [19]. Among these features, the WeChat public platform serves as a vital source of information across various industries, allowing the transmission of information to specific users and interactive channels [19]. Apart from its basic functionalities such as group communication through videos, articles, and other content, it also serves as a medium for all-round communication with users. Importantly, it provides users with convenient access to relevant information at any time and from anywhere. Thus, the WeChat public platform has gained public recognition as an effective means of communication. However, its effectiveness as a tool for preoperative education remains unexplored.

As mentioned above, perioperative anxiety is primarily driven by the uncertainty surrounding disease prognosis as well as fears related to surgery and anesthesia. In response to this issue, our plan involves creating videos focusing on breast cancer prognosis, surgical methods, anesthesia techniques, and other perioperative management knowledge. These videos will be made available to patients via the WeChat public platform, allowing them to access the information whenever and wherever they desire. We anticipate that these measures will contribute to alleviating perioperative anxiety and pain, improving the quality of sleep and life, and facilitating better early postoperative recovery.

## Methods

### Study design, approval, and registration

This prospective randomized controlled trial was conducted at West China Hospital of Sichuan University. The flowchart illustrating the test process can be found in Fig. 1. Patient recruitment began in February 2021. To ensure adherence to proper protocols, this trial adheres to the Standard Protocol Items: Recommendations for Interventional Trials (SPIRIT) 2013 [20, 21]. All registration, interventions, and evaluations are in accordance with the SPIRIT checklist [21]. The Ethics Committee of West China Hospital of Sichuan University has granted approval for this trial (2020–1138), and it has been registered in ClinicalTrials.gov. We have established a project steering committee, consisting of members from the anesthesiology department, breast surgery physicians, and nurses. Anesthesiology researchers are responsible for patient screening, assessment, perioperative management, and follow-up. Breast surgery physicians are in charge of determining the surgical approach and postoperative patient ward management. Breast surgery nurses are responsible for in-person perioperative education on the ward, and all of them are involved in formulating perioperative educational content. Furthermore, monthly group meetings will ensure the quality of patient inclusion. The project management group also will convene monthly meetings to review the progress of the trial. Additionally, the ethics committee will meet every 3 months to assess the conduct of the trial. Given that this is a low-risk intervention, a data monitoring committee is not necessary. There are no plans to collect, evaluate, or store biological specimens for genetic or molecular analysis in the current trial or for future ancillary studies.

**Fig. 1 Fig1:**
[figure not shown]
Consort diagram of study participant flow. STAI, state-trait anxiety inventory; NRS, numeric rating scale; SQS, sleep quality scale; QoR-15, 15-item Quality of Recovery Questionnaire

### Study aim

The aim of our research is to reduce perioperative anxiety in patients diagnosed with breast cancer through preoperative education using the WeChat public platform. This intervention is expected to have a positive impact on early postoperative recovery, prognosis, and long-term life satisfaction.

### Participants

A total of 392 female patients scheduled for elective breast cancer resection at the West China Hospital (Sichuan, China) will be included in this study.

### Inclusion criteria

The inclusion criteria for this study are as follows: female patients undergoing elective breast cancer resection, aged 18 and 80 years, and classified as American Society of Anesthesiologists (ASA) physical status I–III.

### Exclusion criteria

Patients meeting one or more of the following criteria will be excluded from the study: those diagnosed with primary breast cancer combined with malignant tumors of other organs (e.g., lung, kidney, intestine, systemically metastasized breast cancer), patients with tumor recurrence after reoperation, and individuals unable to cooperate with the study due to communication disorders or other reasons.

### Randomization, allocation, and concealment

Upon admission to the hospital, all prospective participants will receive written consent. The consent form will request permission to use their data should they choose to withdraw from the trial as well as allow the research team to share relevant data with participating universities or regulatory authorities. Biological specimens will not be collected or stored as part of this trial. After obtaining informed consent, patients will be randomized into either the WeChat education group or the regular group at a 1:1 ratio. Randomization lists will be generated using the IBM SPSS statistics 23.0 software scheduler computer, and the lists will be concealed from screeners, assessors, and participants. Group allocations and detailed intervention plans will be prepared and sealed in opaque envelopes labeled with each participant’s serial number. These envelopes will be held by the screener responsible for participant screening. When a patient is recruited, the corresponding envelope will be sent to a researcher who will open it and implement the intervention according to the instructions provided (WeChat education or regular preoperative education). Another researcher, responsible for preoperative evaluation and postoperative follow-up, will remain unaware of the patients’ group assignments.

### Patient and public involvement

Researchers actively collaborate with members of the public before conducting the study, working together to plan preoperative educational materials, develop research protocols, and explain the research process and objectives. Throughout the study, researchers also assess the level of discomfort or difficulty associated with the intervention in consultation with the participants. Once the experiment is concluded, the research results are disseminated to the public through various online channels.

### Interventions

Patients who meet the inclusion criteria will be randomly assigned to either the WeChat preoperative education group or the regular group. Two researchers named [name] and [name] will respectively handle preoperative education, preoperative evaluation, and postoperative follow-up.

#### WeChat preoperative education team

In this group, patients are initially assessed by a researcher upon admission to evaluate their anxiety and sleep levels using the State-Trait Anxiety Inventory (STAI) scale and the Sleep Quality Scale (SQS). After the assessment, patients are instructed to follow the WeChat public platform and watch educational videos at their convenience. The content of these videos is collectively decided by the breast surgeon, anesthetists, and ward nurse, including the overall prognosis, surgical approach, postoperative rehabilitation exercises, preparation for anesthesia, anesthesia approach, and possible effects of anesthesia. The videos are presented in a clear and easily understandable manner, ensuring that participants of all ages and educational backgrounds can comprehend the information. Participants can simply click on the video dialogue box within the public platform to play and watch the videos without any restrictions.

#### Regular group

In this group, patients undergo the same anxiety and sleep assessment conducted by the same researcher during the admission process, utilizing the State-Trait Anxiety Inventory (STAI) scale and the SQS. Following the assessment, patients receive oral instruction from the ward nurse, covering the same content as the WeChat education videos (patients in the intervention group also receive oral instructions from the ward nurse).

### Perioperative management

Both groups underwent a routine pre-operative visit and a State-Trait Anxiety Inventory (STAI) test conducted by one researcher on the day before surgery. On the day of surgery, patients entered the operating room where they underwent monitoring of ECG, heart rate, non-invasive blood pressure, and nitrogen dioxide levels. Anesthesia was induced using midazolam 2 mg, propofol 1.5–2.5 mg/kg, sufentanil 0.3 µg/kg, and cis-atracurium 0.2 mg/kg and maintained intraoperatively with propofol, desflurane, or sevoflurane, along with continuous infusion of remifentanil 0.05–0.2 μg/kg/min. Intermittent infusions of sufentanil and cis-atracurium were also administered. At 72 h postoperatively, anxiety scores based on the STAI were evaluated in both groups by the same investigator. Acute pain scores based on the numeric rating scale (NRS) were assessed at 24, 48, and 72 h postoperatively. The use of analgesics and the incidence of nausea and vomiting at 24 h postoperatively were also recorded.

### Data collection

#### Baseline patient characteristics

Patient’s demographics, comorbidity, past surgical history, anxiety scores on admission, and sleep scores will be recorded.

#### Anxiety scores 1 day before and 72 h after surgery

Patients will be assessed for anxiety using the State-Trait Anxiety Inventory (STAI) scale [22, 23] 1 day before surgery and at 72 h after surgery. This 40-item scale is divided into two subscales, each with 20 items. The first part, the “State Anxiety Inventory (S-AI) scale,” evaluates the patient’s current state of anxiety and asks how the participant feels “right now.” The second part, the “Trait Anxiety Inventory (T-AI),” assesses the relatively stable tendency to be anxious [24]. Since this study focused on short-term changes in anxiety levels, the State Anxiety Inventory (S-AI) scale is selected. The total score ranges from 20 to 80, with higher scores indicating more severe anxiety. A score above 40 indicates clinical anxiety [24, 25], and a score exceeding 44 strongly suggests severe anxiety [26].

#### Acute pain assessment at 24, 48, and 72 h postoperatively

At 24, 48, and 72 h after surgery, patients will be evaluated for pain at rest and during activity (coughing or taking three deep breaths) using the NRS (0 = no pain, 10 = worst pain imaginable) [27].

#### Follow-up at 1 week, 1 month, and 3 months (Table 1)

Patients will be followed up via telephone at 1 week, 1 month, and 3 months after surgery. The SQS [28] and the 15-item quality of recovery score (QoR-15 questionnaire) [29] will be used to assess the sleep quality and overall life quality. Each participant will provide at least two telephone numbers to ensure proper follow-up and minimize loss of contact.

**Table 1 Tab1:** Schedule of recruitment, interventions, and assessments

Timepoint	Study period								
	Enrollment	Allocation		Post allocation					
	-d	0	-d_0_	24h	48h	72h	W_1_	m_1_	m_3_
Enrollment									
Case diagnosis	X								
Inclusion criteria	X								
Exclusion criteria	X								
Informed consent	X								
Randomization	X								
Allocation		X							
Interventions									
WeChat education	X								
Videos and/or regular	X		X						
Preoperative visits	X								
Assessments									
Anxiety scores	X		X			X			
PONV	X			X					
Sleep scores	X						X		
Pain assessment	X			X	X	X			
Quality of life scores	X							X	X

According to SPIRIT 2013 statement: defining standard protocol items for clinical trials

*PONV*, postoperative nausea and vomiting

### Outcomes

#### Primary outcome

The primary outcome indicator is the incidence of preoperative anxiety, which is defined as a score of > 40 on the S-AI scale [24].

#### Secondary outcomes

The secondary outcome indicators include:The incidence of severe anxiety (SAI > 44) 1 day before surgery;The incidence of anxiety 72 h after surgery;The incidence of severe anxiety 72 h after surgery;NRS scores for pain at rest and during activity 24, 48, and 72 h after surgery (active status defined as 3 deep breaths or 1 cough);The incidence of nausea and vomiting within 24 h after surgery;Subjective sleep score (SQS) at 1 week postoperatively;Quality of life QoR-15 scores at 1 and 3 months postoperatively.

### Adverse events and safety

Any adverse events, defined as any functional impairment caused by the intervention, will be recorded. Serious adverse events such as Internet/privacy issues targeting breast cancer patients and insurance issues will also be recorded. In the case of any adverse events, appropriate treatment, changes, or discontinuation of the intervention will be offered to the patient. Adverse events must be reported immediately to the principal investigator and the ethics committee to determine whether the patient needs to be withdrawn from the trial.

### Statistics

#### Sample size estimation

The sample size for this study was determined based on the results of our pre-test, which indicated a prevalence of preoperative anxiety in breast cancer patients of 57.1%. It was assumed that the intervention in this study would reduce the incidence of preoperative anxiety by 30%, with a test efficacy of 90% and an alpha of 0.05 (two-sided). The final sample size was determined to be 392 cases, considering a potential loss to follow-up or dropout rate of 10%.

#### Statistical analysis

Statistical analysis was performed using the software SPSS 23.0. The data will be presented as mean ± standard deviation or numbers (percentages). Baseline characteristics will be compared executing the chi-square test or Fisher’s exact test, Student’s *t*-test, or non-parametric tests. The primary outcomes (incidence of preoperative anxiety) will be compared using the chi-square test. Secondary outcomes, including the incidence of anxiety and severe anxiety at 72 h postoperatively, the incidence of nausea and vomiting at 24 h postoperatively, and the incidence of chronic pain at 3 months postoperatively, will be compared between groups using the chi-square test. NRS scores for pain at rest and during activity at 24, 48, and 72 h postoperatively, subjective sleep scores at 1 week postoperatively, quality of life QoR-15 scores at 1 month and 3 months postoperatively, length of hospital stay, and hospitalization costs will be compared using the *t*-test or rank sum test depending on their normality. Subgroup analysis will be conducted for female breast cancer patients who have pre-existing mental/psychological disorders and/or were using psychotropic medications in the final outcomes. A *p*-value < 0.05 will be considered statistically significant.

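### The primary outcome is tested by an unadjusted chi-square although both arms complete the same anxiety scale on admission; the test is valid, but precision is lost and chance imbalance has no prespecified correction

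*Protocol article*

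**What the plan says.** **Primary analysis.** The Statistical analysis section states: "The primary outcomes (incidence of preoperative anxiety) will be compared using the chi-square test". It names no covariate and no adjusted or sensitivity analysis for this outcome. The 72 h anxiety outcomes also get a chi-square test, and the 1-week sleep score gets a *t*-test or rank sum test.

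**Baseline measurement.** For the WeChat arm, the Interventions section says "patients are initially assessed by a researcher upon admission to evaluate their anxiety and sleep levels", using the STAI and the SQS, and only then directs patients to the videos. The Regular group section has the same researcher make the same assessment before the nurse's oral instruction. Under Baseline patient characteristics, "anxiety scores on admission, and sleep scores will be recorded". Table 1 marks anxiety and sleep scores in the enrolment column.

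**Stated use of the baseline.** The only use given is the between-group comparison of baseline characteristics in the Statistical analysis section. It has no stated consequence for the treatment effect.

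**Sample size.** The section gives the anxiety prevalence from the investigators' pre-test, an assumed 30% reduction, and a design "with a test efficacy of 90% and an alpha of 0.05 (two-sided"). It concludes: "The final sample size was determined to be 392 cases", after a 10% allowance for loss.

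**The concern.** The endpoint is a dichotomised S-AI score, and a pre-education score on the same scale is planned for every patient. Such a baseline is usually prognostic for the later score. An analysis that ignores it leaves explainable variation in the comparison, so the estimate is noisier than the data allow.

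Chance imbalance is the second issue. The article describes 1:1 randomisation and mentions no stratification by admission anxiety. The plan tests baseline characteristics for group differences but does not say what follows if admission anxiety differs. The analyst would then have to leave the imbalance alone or decide on adjustment after seeing it. Naming the covariate in advance removes that choice.

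The same reasoning applies to the 72 h anxiety outcomes, which have an admission S-AI, and to the 1-week SQS, which has an admission SQS.

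**Working it through.** **1. Reproduce the plan's sample size.** Inputs from Sample size estimation: control rate 57.1%; 30% reduction, read as relative, so 0.7 × 57.1% = 39.97%; two-sided alpha 0.05; power 90%; loss 10%. The difference is d = 0.1713 and the mean rate is p̄ = 0.48535.

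n per arm = [1.960·√(2p̄(1−p̄)) + 1.282·√(p₁(1−p₁) + p₂(1−p₂))]² / d²
= (1.3853 + 0.8924)² / 0.1713² = 176.8, so 177 per arm, 354 in all.

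Allowing for loss: 354/0.9 gives 394, and 354 × 1.1 gives 390. Both are within 3% of the stated 392. Reading the 30% as percentage points gives 123, which does not match. The 392 is therefore an ordinary two-proportion calculation without a covariate.

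**2. Power of the planned test.** 392 × 0.9 = 352.8, so about 176 evaluable per arm.

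Power = Φ[(0.1713·√176 − 1.3853)/0.6963] = Φ(1.274) = 89.9%. With all 196 per arm it is 92.7%.

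**3. Power with adjustment.** The documents give no correlation ρ between admission and preoperative S-AI, so ρ is an assumption. The model is a normal latent S-AI at both times, cut to give 57.1% and 39.97%. The share of variance in the binary outcome explained by admission S-AI (R²) is about 0.056, 0.159 and 0.323 at ρ = 0.3, 0.5 and 0.7. Adjustment acts roughly like dividing n by (1 − R²). The simulation used 3,000 trials per setting, 176 per arm, and logistic regression on group plus admission score.

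| Assumed ρ | 176/(1 − R²) | Power, formula | Power, simulated | n per arm for 90%: 177 × (1 − R²) |
|---|---|---|---|---|
| 0 | 176 | 89.9% | 89.3% | 177 |
| 0.3 | 187 | 91.5% | 91.6% | 167 |
| 0.5 | 209 | 94.2% | 95.2% | 149 |
| 0.7 | 260 | 97.6% | 98.1% | 120 |

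Simulated chi-square power ranged from 89.2% to 91.1% in these settings, around the formula value of 89.9%. Simulation error near 90% is √(0.9 × 0.1/3000), about 0.5 point. A test on the standardised risk difference had the same power to within 0.2 point.

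**4. Type I error.** With no effect, at ρ = 0.5 and 0.7, the simulated rates were 4.7% and 4.8% for the chi-square test, 5.4% and 5.2% for the logistic test, and 5.5% and 5.2% for the standardised risk difference. Simulation error is about 0.4 point, so all are close to 5%.

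**5. Size of a chance imbalance.** The between-arm difference in mean admission S-AI has standard error √(2/176) = 0.107 SD. The edge of its 95% range is 1.96 × 0.107 = 0.209 SD. The latent density at the cut-off averages 0.389 over the two arms (0.393 and 0.386). The shift in the crude risk difference is about ρ × 0.209 × 0.389: 2.4 points at ρ = 0.3, about 4 at 0.5 and 5.7 at 0.7. The planned difference is 17.1 points.

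**The case against.** The strongest reply is that nothing here is wrong. A chi-square test of a binary endpoint under 1:1 randomisation is valid, matches the basis of the sample size and delivers the planned power. Its error rate already allows for chance baseline differences. All of that stands. A reader might infer from the imbalance figures that the primary result would be biased or the trial underpowered; the documents do not support either reading. What adjustment adds is precision, and protection once a particular imbalance has occurred.

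A reader might also call admission S-AI the strongest predictor of the endpoint, and say that it is collected and then not used. The article ranks no predictors, gives no correlation and does not state the interval between the two assessments. The score does enter the baseline comparison, although that comparison does not adjust the effect.

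A supplementary adjusted analysis could sit in a statistical analysis plan that is not shown. That is fair for supplementary work, but the article itself fixes the unadjusted test as the primary comparison.

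The order of events is a further difficulty. The assessment precedes education in both arms, but it is not clearly placed before the envelope is opened. Table 1 does not settle this, because its enrolment column also marks postoperative items such as nausea and pain. Accepting only scores taken before envelope opening could discard much of the covariate, so the remedy should not depend on that.

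Finally, enrolment ended on 31 March 2022. Changing a primary test when outcomes may already be known carries its own risk of a data-driven choice. This stands and governs the timing of the fix.

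**Conclusion.** The point holds as one of efficiency. The protocol fixes an unadjusted primary test while planning a pre-education score on the same instrument for both arms. The planned test is sound and has about 90% power. Adjustment would raise this to about 91–98% if the admission-to-preoperative correlation lies between 0.3 and 0.7, and would cost nothing at zero. The existence of the gap is certain from the text. The size of the gain rests on the assumed correlation, a normal latent score, the design rates and 176 evaluable patients per arm. The trial remains interpretable without the change, which is worth making because it is nearly free.

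**What to change.** - Before unblinded outcome data are seen, and with the change dated, make the primary analysis a logistic regression of S-AI above 40 (day before surgery) on group and continuous admission S-AI.
- Report the standardised (marginal) risk difference with its 95% CI, which targets the same quantity as the crude comparison. Keep the chi-square test as a supportive analysis.
- Use every admission score taken before education began. Keep patients with a missing admission score in the analysis by simple imputation of the covariate, for example the overall mean.
- If some scores are known to have been taken after the envelope was opened, show in a sensitivity check how the result changes when they are treated as missing.
- Adjust the 72 h anxiety outcomes for admission S-AI, and the 1-week SQS for admission SQS, in the same way.
- If outcomes have already been seen, leave the chi-square test as primary and report the adjusted result as a labelled sensitivity analysis.

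**Cost:** a documented change to the analysis text, plus checks on missing admission scores and, where recorded, their timing. No new data or patients are needed.

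### The 1-week sleep score is compared without the admission score on the same scale, so this valid secondary comparison is less precise than the data allow

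*Protocol article*

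**What the plan says.** **Analysis.** Statistical analysis assigns a t-test or rank sum test, chosen by normality, to a group of outcomes that includes "subjective sleep scores at 1 week postoperatively, quality of life QoR-15 scores at 1 month and 3 months postoperatively". No baseline term is named. The only use left for admission values is the between-group comparison of baseline characteristics.

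**Sleep on admission.** For the intervention arm, the section WeChat preoperative education team has a researcher "evaluate their anxiety and sleep levels using the State-Trait Anxiety Inventory (STAI) scale and the Sleep Quality Scale (SQS") on admission, and the instruction to watch the videos comes afterwards. The section Regular group prescribes the same assessment by the same researcher before the nurse's teaching. Baseline patient characteristics confirms this: "demographics, comorbidity, past surgical history, anxiety scores on admission, and sleep scores will be recorded".

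**QoR-15 and pain.** Neither is in that list or in the two admission descriptions. In Table 1, however, the row "Quality of life scores" carries a mark under Enrollment as well as at 1 and 3 months, and the pain row carries one under Enrollment as well as at 24, 48 and 72 h.

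**The concern.** The admission SQS is measured on the outcome's own scale, before either arm has been taught, and it is already planned for every patient. Leaving it out keeps stable differences between patients in the error term of the 1-week comparison, and the confidence interval is wider than it need be. The protocol names better sleep among its aims, in the Introduction and at the end of the Discussion. The sample size was set for the primary anxiety outcome alone, so no power is stated for sleep and precision there is not assured by design.

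This is not a detail left open for a later analysis plan: the article names the test for this outcome. The point does not touch the primary outcome.

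**Working it through.** **1. The plan's own sample size.** Inputs from Sample size estimation: "prevalence of preoperative anxiety in breast cancer patients of 57.1" percent; the intervention is assumed to "reduce the incidence of preoperative anxiety by 30%, with a test efficacy of 90% and an alpha of 0.05 (two-sided"); and "The final sample size was determined to be 392 cases, considering a potential loss to follow-up or dropout rate of 10" percent. Reading the 30% as relative, p1 = 0.571 and p2 = 0.571 × 0.7 = 0.3997.

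n per arm = [1.960 × √(2 p̄(1 − p̄)) + 1.282 × √(p1(1 − p1) + p2(1 − p2))]² / (p1 − p2)², with p̄ = 0.48535. This gives 177 per arm, 354 in total. Allowing for 10% dropout gives 394 (dividing by 0.9) or 390 (multiplying by 1.1). With p2 rounded to 0.40, n is 178 per arm, and 178 × 1.1 = 195.8, so 196 per arm and exactly 392. The figure reproduces. It belongs to the primary outcome and matters here only for the number of patients: allocation is "randomized into either the WeChat education group or the regular group at a 1:1 ratio", so 392 / 2 = 196 per arm, and 196 × 0.9 ≈ 176 evaluable per arm.

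**2. Precision for 1-week SQS.** Let σ be the SD of the 1-week score and ρ its correlation with the admission score within arm. The protocol gives neither, so results are in SD units over an assumed range of ρ.

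- Unadjusted variance of the difference: 2σ²/n. With n = 176 the standard error is √(2/176) = 0.1066 SD.
- Adjusted variance: 2σ²(1 − ρ²)/n.
- Interval width ratio: √(1 − ρ²).
- Equivalent n per arm: 176 / (1 − ρ²).
- For illustration, take a difference that has 80% power unadjusted: (1.960 + 0.842) × 0.1066 = 0.299 SD. Its power after adjustment is Φ(2.802/√(1 − ρ²) − 1.960).

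| Assumed ρ | Variance falls by | Interval narrower by | 176 per arm worth | 80% power becomes |
|---|---|---|---|---|
| 0.2 | 4% | 2% | 183 | 82% |
| 0.3 | 9% | 5% | 193 | 84% |
| 0.5 | 25% | 13% | 235 | 90% |
| 0.7 | 49% | 29% | 345 | 97.5% |

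**3. Is there a QoR-15 or pain baseline?** The prose is consistent: the two admission descriptions and the baseline list give only anxiety and sleep, and QoR-15 appears under telephone follow-up. Against this stands the Enrollment column of Table 1. That column marks every row except Allocation. It includes postoperative nausea and vomiting, which cannot be observed before surgery, and preoperative visits, which Perioperative management places on the day before surgery. A column filled in this way is weak evidence that any particular score was scheduled at enrollment.

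**The case against.** The strongest reply is that nothing here is an error. Under 1:1 randomization the unadjusted test is unbiased and keeps its type I error rate. Chance imbalance in admission sleep is ordinary sampling variation, which the test already allows for, and the planned baseline comparison would show it. That stands: this is an efficiency point on one secondary outcome at one time point.

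It is also fair that the size is assumed. Admission SQS precedes cancer surgery and the follow-up score comes a week after it, so the correlation may be modest; at 0.2 the gain is negligible. The 80% starting power is illustrative only. The factor 1 − ρ² describes the linear model and does not carry over directly to the rank sum test that the plan allows, so a remedy must cover the non-normal case.

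A reader might infer from Table 1 that the QoR-15 and pain comparisons lose precision in the same way, or that a scheduled QoR-15 baseline is being thrown away. The documents do not support that. It would need a baseline that the prose nowhere mentions and that rests only on an unreliable column. Nor does the missing adjustment make the sleep result biased or invalid.

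What the reply does not remove is that a same-scale covariate is collected in both arms and the named test ignores it.

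**Conclusion.** The point holds for the 1-week SQS. The planned comparison is valid but less precise than the collected data allow. The loss runs from trivial (4% of variance at ρ = 0.2) to substantial (49% at ρ = 0.7), and the documents do not show where in that range the truth lies. The figures assume a linear relation between admission and 1-week scores and about 176 evaluable patients per arm after the plan's 10% dropout.

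For QoR-15 and pain, only an inconsistency between Table 1 and the baseline list is established. It is clerical, and no loss of precision is claimed. Overall this is an inexpensive improvement to a secondary analysis, with no bearing on the primary outcome.

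**What to change.** In Statistical analysis, take the 1-week SQS out of the t-test or rank sum group. Analyse it with a linear model containing arm and admission SQS, and report the adjusted mean difference with its 95% confidence interval. State that a rank-based ANCOVA will be used for the test if the scores are clearly non-normal. Add a simple rule for patients with no admission score, such as mean imputation of the covariate. That rule is the only real downside; no new data are needed. The change should be fixed before the groups are compared, if that is still possible.

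Separately, reconcile the Enrollment column of Table 1 with Baseline patient characteristics for QoR-15, pain and postoperative nausea and vomiting. If QoR-15 or NRS scores were in fact taken at enrollment, add them to the baseline list and adjust their follow-up comparisons in the same way. If they were not, delete the marks. Trial status records that enrollment closed on March 31, 2022, so this can only document what was collected, not recover a missing baseline.
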